### Participants

Since seniors living in subsidised housing managed by community housing are typically defined as ‘senior’ if they are 55 years or older, and individuals with low socioeconomic status report poorer health^27^and increased health behaviour risk factors,^28^ CHAP-EMS has defined our study population as individuals 55 years and older residing in selected subsidised apartment buildings under the management of the local City Housing department. Only subsidised seniors’ buildings in which 60% or more of the apartment units are occupied by residents 55 years or older will be chosen. All residents 55 years and older will be included as potential participants for the individual level outcomes. Those individuals who have been staying in the buildings for less than 3 months (as visitors or guests) will be excluded. Participation in the CHAP-EMS programme will be voluntary. Names of participants will remain secure in the CHAP-EMS database and will not be disclosed to any third party or City Housing official.

### Allocation of intervention

First, the buildings will be matched into similar pairs based on geographic location, numbers of units within the building, proportion of units occupied by seniors, existing EMS call rate (number of calls/100 apartment units) in the 2 years prior to the intervention period and the types of social programmes offered to residents. Then, for each matched pair, one building will be randomised to receive the intervention and the other will not receive the intervention (control group). Block randomisation will be used with random allocation of the intervention within each block of two buildings.

Residents of the intervention buildings will have access to the CHAP-EMS programme, in additional to their usual medical care and wellness programmes, while residents of control buildings will only have access to their usual medical care and wellness programmes. Since randomisation is occurring at the building-level, it is not expected that providing usual care as the control condition will impact study recruitment, results or interpretation.

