### Sample size

Given that our main outcome will be rates of calls per 100 residents per year, we calculated our sample size using the formula for the Poisson test. Based on data from the Hamilton Paramedic Services, the average rate of calls for our pilot sample was 44.06 EMS calls per year per 100 residents older than 65 years. If we assume a difference of 10% (a difference of 4.4 EMS calls per 100 residents per year) between the intervention and control groups, with 0.8 β and α of 0.05, we would need a sample of 131 per group. This is a conservative estimate of effect size since the pilot study showed a 25% reduction in EMS calls.^26^ Also, a difference of 10% is considered operationally significant by Hamilton Paramedic Services (personal communication with [name]). This is likely to be significant in other Ontario localities as well.

The overall sample size will be a minimum of 700 participants per arm (intervention or control) in 12 or more intervention buildings across all sites. Considering the Design Effect (cluster sampling by buildings), we can accommodate an intracluster correlation coefficient (ICC) of up to 2.5% given our proposed sample size. There is no literature regarding an ICC for a similar study.

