### Primary and secondary outcome measures

The primary outcome of EMS call rate (number of calls for building made by residents aged 55 years or older per 100 residents aged 55 years or older in the subsidised seniors’ building) will be available for each building from the EMS administrative database. The primary outcomes of change in measured systolic and diastolic BP, and difference in 10-year diabetes risk (CANRISK score), will be available from the measurements entered by the paramedics into the study database. The secondary outcomes will be difference in health perceptions, behaviours, intentions regarding behaviours, health literacy and knowledge of resources, measured by interviewer-led survey preintervention and postintervention; and difference in health-seeking behaviour (eg, number of ED visits/population 55 years and older), which will be based on administrative databases.

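### The sample size is planned on a call rate for residents over 65 and pairs are matched on calls per apartment unit, but the primary outcome is a rate in residents 55+, and no conversion is given

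*Protocol article*

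**What the plan says.** Four places in the protocol article bear on the call rate.

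- **Participants.** The trial has "defined our study population as individuals 55 years and older residing in selected subsidised apartment buildings". A building qualifies if "60% or more of the apartment units are occupied by residents 55 years or older", so up to 40% of units may have no resident of that age.
- **Allocation of intervention.** One pairing factor is the "existing EMS call rate (number of calls/100 apartment units) in the 2 years prior to the intervention period". The denominator is units, and no age limit on the caller is stated. The same sentence also pairs on location, social programmes and "numbers of units within the building, proportion of units occupied by seniors".
- **Sample size.** The planning input is that "the average rate of calls for our pilot sample was 44.06 EMS calls per year per 100 residents older than 65 years". The target is a 10% reduction, given as 4.4 calls per 100 residents per year. The result is stated as "with 0.8 β and α of 0.05, we would need a sample of 131 per group".
- **Primary and secondary outcome measures.** The outcome is the "number of calls for building made by residents aged 55 years or older per 100 residents aged 55 years or older".

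No section converts one basis to another or explains why they differ.

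**The concern.** Two separate consequences follow.

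First, the planning rate describes people over 65, while the analysed population starts at 55. Residents aged 55 to 65 contribute calls and denominator to the outcome but not to the planning figure. For a given percentage reduction, the rate determines the required size directly, so a rate from another population leaves the stated size without a proper basis.

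Second, the pairing variable is not the pre-period value of the outcome. Two buildings can agree on calls per unit and still differ in calls per 55+ resident, because the number of 55+ residents per unit differs or because a different share of calls comes from younger people. Pairing gains precision to the extent that it makes buildings alike on the outcome, and a looser link means a smaller gain.

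**Working it through.** **The plan's own figure.** Inputs from the Sample size section: r1 = 0.4406 per person-year; a 10% reduction, so r2 = 0.3965; 0.8 read as power; alpha 0.05. With the usual two-sample Poisson formula, two-sided,

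n per group = (1.960 + 0.842)² × (r1 + r2) / (r1 − r2)² = 7.849 × 1.9 / (0.01 × 0.4406) = 3,385.

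The stated figure is 131. One-sided, one-sample, square-root, log-rate and two-proportion variants, and reading 0.8 literally as beta, did not reproduce it either. That is a separate and larger problem. The step below therefore uses only ratios, which apply to whatever starting size is correct.

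**Effect of the age basis on size.** With r2 = 0.9 × r1, the formula reduces to n = 7.849 × 190 / r1 with r1 per 100 residents, so n is proportional to 1/r1. The document gives no 55+ rate; the rates below are assumptions.

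| 55+ rate per 100 per year (assumed) | Ratio 44.06/rate | Stated 131 rescaled |
|---|---|---|
| 50 | 0.88 | 115 |
| 44.06 | 1.00 | 131 |
| 40 | 1.10 | 144 |
| 35 | 1.26 | 165 |
| 30 | 1.47 | 192 |

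This scaling holds the relative reduction at 10%, which is how the section justifies its target. If the absolute 4.4 calls were held instead, n would be proportional to (2 × r1 − 0.044), with r1 per person-year. At a rate of 30 per 100 the ratio would be (0.60 − 0.044) / (0.8812 − 0.044) = 0.556 / 0.837 = 0.66, a fall. The restated calculation should say which is fixed.

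**Effect of the matching basis.** For one building,

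outcome rate per 100 = calls per 100 units × share of calls from 55+ ÷ (proportion of senior units × 55+ residents per senior unit).

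Pairing covers the first term and the proportion of senior units. It leaves the share of calls from 55+ and the residents per senior unit free. Each illustration takes two buildings with 50 calls per 100 units and the same senior proportion; all figures are assumed.

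- All units senior, all calls from 55+, 1.0 versus 1.4 residents per unit: 50/1.0 = 50.0 versus 50/1.4 = 35.7, which is 29% lower.
- 70% senior units, one resident each, 90% versus 70% of calls from 55+: 50 × 0.9/0.7 = 64.3 versus 50 × 0.7/0.7 = 50.0, which is 22% lower.
- 60% senior units; 1.0 resident per senior unit with 60% of calls from 55+, versus 1.2 with 70%: 50 × 0.6/0.6 = 50.0 versus 50 × 0.7/0.72 = 48.6, which is 3% lower.

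The gap within a pair can therefore be small or well above the 10% target. The document does not allow its typical size to be estimated.

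**The case against.** The case on the other side is substantial.

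- *A matching variable need not equal the outcome.* This stands. A correlated building-level rate is a legitimate choice, and random allocation within each pair keeps the comparison unbiased. A reader might infer that the mismatch biases the result; it does not.
- *Pairs are also similar in unit count and senior proportion.* This stands in part. The 40% allowance for other units is a limit on eligibility and does not describe a difference between paired buildings. Residents per unit and caller age remain unmatched.
- *The missing age limit is silence in a condensed article.* This is fair: the matching rate may have been restricted by age. The unit denominator is explicit, however.
- *The baseline comparison is not harmed.* This stands. A reader might infer that it is, but Control of bias promises at least one year of earlier data for the EMS call outcome itself, and Data analysis examines pre-intervention and intervention periods. The pairing rate is not the analysis baseline.
- *The age basis does not decide whether 700 per arm is enough.* This depends on cluster size. With 12 buildings per arm (700/12, about 58 each) and the stated 2.5% ICC, the design effect is 1 + 57.3 × 0.025 = 2.43, and even 192 × 2.43 = about 467 is below 700. But the 2.5% ceiling fits about 175 residents per building, since 131 × (1 + 174 × 0.025) = 701, and there no slack remains. If 3,385 is the right starting point, 700 is short on any age basis.
- *No 55+ rate is given.* This stands. A reader might infer that the trial is under-sized because younger seniors call less often; the document shows neither that nor the reverse.

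**Conclusion.** The inconsistency is real and lies in the current text. The planning rate is for residents over 65, the population and outcome are 55+, the matching rate is per apartment unit, and nothing links them.

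The stated sample size therefore lacks a planning rate for the population it serves. Under a fixed 10% relative reduction, the required number would change by the ratio of 44.06 to the 55+ rate: about +10%, +26% or +47% at assumed rates of 40, 35 or 30, and a decrease at any rate above 44.06. Neither direction nor size can be established from the document.

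The matching mismatch is a matter of precision only, partly offset by the other pairing factors, and its cost cannot be quantified here. The point merits correction because the remedy is modest; it does not undermine the validity of the randomised comparison.

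**What to change.** 1. In Sample size, replace the over-65 rate with the yearly rate on the outcome definition (calls by 55+ residents per 100 such residents). Recalculate the required number, stating whether the 10% relative or the 4.4 absolute difference is held fixed. If only the over-65 rate can be obtained, say so and show the size over a range of 55+ rates.
2. Compute each building's pre-intervention rate on the same definition from the EMS data. Use it as the call-rate factor in matching. Where pairs are already fixed, specify it as a baseline covariate in the primary building-level GEE.
3. If calls per unit is kept for matching, state whether calls are limited by age and why that basis was chosen.

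The cost is re-tabulation of past calls by caller age and of past 55+ resident counts by building. The outcome section says the 55+ rate will be available for each building from the EMS administrative database, and earlier data are already planned, so no new source appears to be needed for the calls. The document does not state how complete caller age or historical resident counts are, so this should be checked before the covariate is fixed.

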### Sample size

Given that our main outcome will be rates of calls per 100 residents per year, we calculated our sample size using the formula for the Poisson test. Based on data from the Hamilton Paramedic Services, the average rate of calls for our pilot sample was 44.06 EMS calls per year per 100 residents older than 65 years. If we assume a difference of 10% (a difference of 4.4 EMS calls per 100 residents per year) between the intervention and control groups, with 0.8 β and α of 0.05, we would need a sample of 131 per group. This is a conservative estimate of effect size since the pilot study showed a 25% reduction in EMS calls.^26^ Also, a difference of 10% is considered operationally significant by Hamilton Paramedic Services (personal communication with [name]). This is likely to be significant in other Ontario localities as well.

The overall sample size will be a minimum of 700 participants per arm (intervention or control) in 12 or more intervention buildings across all sites. Considering the Design Effect (cluster sampling by buildings), we can accommodate an intracluster correlation coefficient (ICC) of up to 2.5% given our proposed sample size. There is no literature regarding an ICC for a similar study.

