Studies have shown that older adults account for more than a third of all Emergency Medical Service (EMS) calls related to cardiopulmonary conditions, diabetes and falls.^11–14^ This may be due to the fact that older adults with high comorbidity (>3 chronic conditions) report poorer health, take more prescription medications and have the highest rate of healthcare visits.^15^ Data from Hamilton Paramedic Service indicate that tenants in ‘seniors’ buildings’ in underserved areas of lower socioeconomic status in Hamilton, a medium sized city in Canada, with a population of just over 500 000 people, are the most frequent callers to the emergency 911 medical service. On average, each paramedic visit and subsequent mandatory hospital emergency department (ED) visit costs around $1044 Canadian dollars.^16^
^17^ Therefore, interventions that reduce the escalation of EMS calls and ED visits could provide potential savings to the healthcare system. Current government approaches being explored include looking for programmes that reallocate existing resources to decrease the use of ED resources.

Studies expanding the role of paramedics to include health promotion and referral to appropriate health service providers have been successfully implemented in other settings. However, this research has been limited to case studies, mostly in rural Australia.^18–20^ Previous studies have shown that paramedics were seen as an underused human resource in rural and remote areas.^18^ Expanded roles included both clinical and primary care, such as community education and engagement, preventive services, treatment of minor illness (and locally endemic conditions) and promotion of lifestyle change to prevent and manage chronic disease.^18^
^20^ A qualitative evaluation showed that these roles were acceptable to the paramedics and were appreciated by the community. Another study, conducted in the UK, evaluated expanding the roles of paramedics in responding to calls from the elderly living in urban areas;^19^ paramedics were given the additional role of referring patients to a general practitioner, district nurse and/or community social services, when needed.

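### The sample size takes the variance of EMS calls as Poisson apart from a building design effect, so even a correctly computed Poisson size would probably be too favourable

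*Protocol article*

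**What the plan says.** All references are to the protocol article.

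- **Sample size, method and rate.** The method is given as "we calculated our sample size using the formula for the Poisson test". The input rate is that "the average rate of calls for our pilot sample was 44.06 EMS calls per year per 100 residents older than 65 years". The target is a 10% relative difference, and the result is stated as "with 0.8 β and α of 0.05, we would need a sample of 131 per group".
- **Sample size, planned numbers.** "The overall sample size will be a minimum of 700 participants per arm (intervention or control) in 12 or more intervention buildings across all sites". The only allowance for extra variance is a design effect for building, said to accommodate an ICC of up to 2.5%. No dispersion parameter is given.
- **Primary and secondary outcome measures.** The EMS outcome is the number of calls made by residents aged 55 or older, per 100 such residents. It counts calls, not callers.
- **Introduction.** In explaining older adults' share of EMS calls, it says that "older adults with high comorbidity (>3 chronic conditions) report poorer health, take more prescription medications and have the highest rate of healthcare visits".
- **Allocation of intervention.** Buildings will be paired on several features, including "existing EMS call rate (number of calls/100 apartment units) in the 2 years prior to the intervention period".
- **Control of bias.** At least one year of call data before the intervention will be collected.

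**The concern.** A Poisson formula sets the variance of the call count equal to its mean. The two arms contain different residents. If residents differ in their underlying call rates, the arms differ by chance in how many frequent callers they hold, and the difference between arms varies more than Poisson.

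The building design effect does not repair this by itself. The factor 1 + (m − 1) × ICC multiplies the per-resident variance. If that variance starts at the Poisson value when the true one is larger, the product is too small.

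The practical risk lies in the correction. Once 131 is found to be wrong, it is natural to redo the same Poisson formula, or to fall back on the pilot's 25% reduction, for which Poisson power at 700 per arm looks comfortable. Both steps would carry the same optimistic variance forward.

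**Working it through.** **Inputs from the article.** Control rate L = 0.4406 calls per resident-year; reduction d = 10% (25% in the pilot); α = 0.05; 1:1 allocation; one year of intervention; 700 per arm.

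**Inputs assumed.** A two-sided test; 0.8 read as power; a variance/mean ratio φ between 1 and 3. The article gives no value for φ.

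**1. The plan's own figure.** The two-group Poisson formula is n = (1.960 + 0.842)² × (L₁ + L₂)/(L₁ − L₂)². With L₁ = 0.4406 and L₂ = 0.3965, this is 7.849 × 0.8371/0.04406² ≈ 3,385 per arm, not 131. A value near 131 appears only from a one-sided, one-sample formula with 0.8 taken literally as β (20% power): (1.645 − 0.842)² × 0.3965/0.04406² ≈ 131.8. That is not the two-group comparison described. The error is a separate and larger point, so the rest starts from 3,385.

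**2. Effect of extra-Poisson variance on size.** n scales with φ: 5,078, 6,770 and 10,155 per arm at φ = 1.5, 2 and 3, before clustering.

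**3. Power at 700 per arm.** z = dL/√(φL(2 − d)/700), and power = Φ(z − 1.960). At φ = 1, z is 0.04406/√(0.4406 × 1.9/700) = 1.274 for a 10% reduction and 0.1102/√(0.4406 × 1.75/700) = 3.32 for 25%. Other values divide by √φ. The last column solves z = 2.80 for d.

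| φ | Power, 10% reduction | Power, 25% reduction | Reduction detectable with 80% power |
|---|---|---|---|
| 1 | 24.6% | 91% | 21% |
| 1.5 | 17.9% | 77% | 26% |
| 2 | 14.5% | 65% | 30% |
| 3 | 11.0% | 48% | 35% |

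The table leaves out building clustering and any gain from matching or baseline adjustment.

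**4. Is a ratio of this order conceivable?** Two made-up distributions with mean 0.44 serve as illustration only.
- If 24% of residents call exactly once and 5% exactly four times, the variance is 0.24 + 0.05 × 16 − 0.44² = 0.846, a ratio of 0.846/0.44 = 1.9.
- If those are instead underlying yearly rates (1 and 4, with 0 for the rest) and calls are Poisson around them, the ratio is 1 + 0.846/0.44 = 2.9. A simulation of two arms with unequal rates and zero ICC also gave a between-arm variance about 2.9 times Poisson.

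**5. What baseline data could recover.** Suppose the same residents stay and keep the same rates. Write v = φ − 1. Adjusting for a two-year baseline leaves a ratio of 1 + 0.5v/(v + 0.5), so 1.5, 2 and 3 become 1.25, 1.33 and 1.40. Power for a 25% reduction is then 84%, 82% and 80%. Full persistence is the favourable extreme.

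**The case against.** **Unequal rates do not by themselves break the Poisson model.** Independent Poisson counts with different means still sum to a Poisson count, and EMS calls are to be analysed at building level only. A simulated fixed building of 58 residents with very unequal rates had a yearly variance/mean ratio of 1.00. This stands for one building with unchanging residents. It does not settle a comparison of arms holding different residents, where the mix of callers differs by chance. It does show that repeat calling and building differences cannot be treated as cleanly separate sources.

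**Matching and baseline data reduce the variance.** This stands. For a given ratio, the table is pessimistic in that respect, although adding building clustering would push the other way. The stated sample size takes credit for neither matching nor baseline adjustment.

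**The size is assumed.** This also stands. The Introduction's remark is about older adults in general and healthcare visits. It supports the direction, not an amount, and does not show that EMS calls are concentrated among a few residents of these buildings.

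**There is slack on the plan's own numbers.** 700/131 = 5.34. With 12 buildings per arm (about 58 residents each), an ICC of 2.5% uses 1 + 57.3 × 0.025 = 2.43, which leaves a factor of about 2.2. That slack exists only because 131 is far too small.

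**25% is not the design effect.** Correct. The article designs for 10% and states no power for 25%. At 10%, Poisson power is already about 25%, so dispersion worsens a calculation that has already failed.

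**Conclusion.** The point holds in direction and is secondary to the error in 131. The between-arm variance of calls will probably exceed Poisson, and the plan's only allowance is a building design effect. Restating the size by a correct Poisson formula would therefore still be too favourable. Over assumed ratios of 1 to 3, power at 700 per arm falls from 24.6% to 11.0% for the 10% reduction and from 91% to 48% for 25%, without clustering and without gains from matching or baseline adjustment.

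A reader might infer three stronger things that the document does not support:
- That the Poisson formula is wrong simply because residents' rates differ. It is the comparison of different residents between arms that adds variance.
- That the trial cannot detect the pilot's 25% reduction. This depends on an unknown ratio, on clustering, and on how much matching and baseline data recover.
- That the planned GEE analysis is invalid. The point concerns the stated sample size only.

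**What to change.** When correcting 131 in the Sample size section:

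1. Replace the Poisson variance with the total extra-Poisson variance of building-level call counts, estimated from the two-year pre-intervention records to be used for matching. Compare buildings with each other; year-to-year change within one stable building can look Poisson even when residents differ.
2. If the analysis will use pairs or adjust for baseline calls, estimate the variance within pairs or after that adjustment. Pairs chosen on these same rates will look more alike than they will in the trial year, so it is safer to match or adjust on one year and estimate the remaining spread in the other.
3. Do not also apply a separate ICC to that estimate. Building totals give the combined excess variance and cannot separate repeat callers from building differences.
4. State the reduction detectable with 80% power at 700 per arm over a range of dispersion, because an estimate from about 12 pairs will be imprecise.

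The cost is a little analysis of records that the trial already plans to obtain, and a less favourable stated figure. No extra residents are needed.

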### Data analysis

We will use an intention-to-treat analysis and generalised estimating equations (GEE) assuming a Poisson distribution and an exchangeable correlation structure within a building to evaluate healthcare utilisation, BP and risk assessment scores, as well as to identify factors contributing to these outcomes. Rate of EMS calls will be analysed at the building-level only, using GEE. We will perform pairwise comparisons of outcomes for each month during the preintervention and intervention periods. We will identify trends in the outcomes during the preintervention and postintervention observation periods. Subgroup analysis by clusters (each building) and by location will be performed. The HABiT survey data will be summarised as a numerical score representing the participants’ perceptions and behaviours regarding CVD and diabetes, and analysed with GEEs. The intracluster correlation coefficient (ICC) will be computed to determine the effect of clustering (by the building the participants reside in) on the participants’ scores. Other outcomes will be analysed using descriptive statistics.

All analyses requiring health administrative data will be performed in a two-step process. First, CHAP-EMS data with identifiers will be securely transferred to ICES for health record linkage, as per the participant consent form. Once linked, the data set will be de-identified for subsequent analysis. All analyses will be performed using SPSS V.20. Statistical significance will be set at α=0.05 and adjusted using the Bonferroni method for secondary analyses. Results will be reported as rate ratios, 95% CIs and associated p values.

Twice a month, the CHAP-EMS data will be reviewed and analysed to assess for errors in data entry, and assure fidelity to the planned intervention (eg, monitor referral patterns by EMS personnel and proper use of the screening tools). This trial did not warrant formal externally managed data monitoring, or a formal committee, due to its minimal risks. Instead, interim analysis will be conducted on the process measures to evaluate intervention recruitment and implementation, and to provide regular reports to local stakeholders (eg, EMS, public health, local housing). Collaborative research agreements with local partners (eg, housing) specify that aggregate data will be shared with these local stakeholders. Individual data will not be released without written permission from the participant.

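### The stated 131 per group for a 10% reduction in EMS calls does not follow from its own inputs (about 3,385 two-sided), and the minimum of 700 per arm is underpowered for that effect

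*Protocol article*

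**What the plan says.** All inputs stand in the Sample size section of the protocol article. The method is given as "we calculated our sample size using the formula for the Poisson test". The reference rate is "44.06 EMS calls per year per 100 residents older than 65 years". The effect is set by "If we assume a difference of 10% (a difference of 4.4 EMS calls per 100 residents per year) between the intervention and control groups", and the error rates by "with 0.8 β and α of 0.05". The result is "we would need a sample of 131 per group". The section calls 10% a conservative effect, because the pilot saw a 25% reduction, and says that the Hamilton paramedic service regards 10% as operationally significant.

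The next paragraph sets the size of the trial: "The overall sample size will be a minimum of 700 participants per arm (intervention or control) in 12 or more intervention buildings". It adds that this size can accommodate an ICC of up to 2.5%, and that no ICC from a similar study is available. It gives no power for 700 per arm. The section does not say whether the test is one-sided or two-sided. The Data analysis section sets α at 0.05 and says "Results will be reported as rate ratios, 95% CIs and associated p values", which fits a two-sided test.

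**The concern.** At 44.06 calls per 100 residents, 131 residents yield about 58 calls in a year, against about 52 after a 10% reduction. A gap of six between two Poisson counts of that size is well within chance, so 131 cannot be right for 80% power.

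It matters because this is the only power calculation in the article and it concerns the outcome that the section calls the main one. A reader will take the trial as able to detect the 10% difference that it names as operationally significant. If it is not, a non-significant result says little about whether a 10% reduction occurred.

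**Working it through.** **Inputs.** From Sample size: λ₁ = 0.4406 calls per resident-year; 10% lower gives λ₂ = 0.39654; difference 0.04406; α = 0.05; the stated β of 0.8 read as power 0.80; at least 700 per arm and 12 intervention buildings; ICC up to 0.025. From Study design and Allocation of intervention: one year of programme, so one resident contributes one resident-year, and 1:1 allocation within pairs, so 12 control buildings as well.

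**1. Trying to reproduce 131.** For two Poisson rates, n per group = (z_α + z_power)² × (λ₁ + λ₂) / (λ₁ − λ₂)².

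- Two-sided: (1.960 + 0.842)² × 0.83714 / 0.04406² = 7.849 × 0.83714 / 0.0019413 ≈ 3,385.
- One-sided: (1.645 + 0.842)² × 0.83714 / 0.0019413 ≈ 2,666.
- Ratios to the stated figure: 3,385 / 131 = 25.8 and 2,666 / 131 = 20.4.

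Other forms do not reach 131 either:

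| Variant | n per group |
|---|---|
| Log rate ratio, two-sided | 3,388 |
| Square-root transform, two-sided | 3,383 |
| Two proportions, two-sided | 1,967 |
| One-sample test, two-sided / one-sided | 1,727 / 1,355 |
| β literally 0.8 (power 20%), two-sided / one-sided | 540 / 279 |
| 25% reduction, 80% power, two-sided / one-sided | 499 / 393 |

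One calculation on the stated rate does land close: a one-sample, one-sided test for a 10% *increase* at 20% power gives 131.8. It is not a comparison of two groups at 80% power, so it does not support the figure.

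**2. What 131 per group delivers.** Power = Φ(0.04406 / √(0.83714 / 131) − 1.960) = Φ(0.551 − 1.960) ≈ 8% for a 10% reduction. The reduction d detectable with 80% power solves d² / (2 − d) = 7.849 / (0.4406 × 131) = 0.136, so d ≈ 46%.

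**3. What the minimum plan delivers.** Residents per building: 700 / 12 = 58.3. Design effect at ICC 0.025: 1 + 57.3 × 0.025 = 2.43, so the effective size is 700 / 2.43 ≈ 288 per arm. Power = Φ(0.04406 / √(DE × 0.83714 / 700) − z_α). At DE 1 the first term is 1.274; at DE 2.43 it is 0.817.

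| ICC | Power for 10%, two-sided | One-sided | Reduction detectable with 80% power (two-sided) | Power for 25%, two-sided |
|---|---|---|---|---|
| 0 | 25% | 36% | 21% | 91% |
| 0.01 | 17% | 27% | – | 75% |
| 0.025 | 13% | 20% | 32% | 57% |

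Simulating the exact conditional test without clustering gives 23% at 700 per arm and 80% at 3,385. With the design effect of 2.43, a 10% reduction would need 3,385 × 2.43 ≈ 8,240 per arm.

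**4. The ICC statement.** If 700 is meant to be 131 inflated for clustering, the design effect is 700 / 131 = 5.34. An ICC of 2.5% then needs 1 + 4.34 / 0.025 ≈ 175 residents per building, that is about four buildings per arm. With 12 buildings of 58.3, the same design effect corresponds to an ICC of 4.34 / 57.3 ≈ 7.6%. So even with 131 taken as correct, 2.5% does not match the stated number of buildings.

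**The case against.** No variant on the stated inputs defends 131 as a two-group size at 80% power. The fair objections concern how far the conclusion reaches.

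- **The plan does not state 80% power at 700 per arm.** A reader might infer that it does. The error rates are attached to the 131 only; adequacy of 700 is implied by the ICC remark. This stands.
- **Nor does it say that 700 was derived from 131.** That is a natural inference, since no other base size is given, but step 4 shows that the figures do not connect at 12 buildings. This stands.
- **An ICC of 2.5% is a ceiling, not an expected value.** The 13%, 32% and 57% figures describe that ceiling, and the section says that no ICC for a similar study is known. This stands.
- **700 and 12 are minimums.** The outcome counts calls by all residents aged 55 or older, so the denominator may exceed 700, and up to eight buildings in each of five named regions would give 20 per arm. This stands, but does not close the gap. With 2,000 per arm and no clustering, power for 10% is Φ(0.04406 / √(0.83714 / 2,000) − 1.960) ≈ 58%. At ICC 2.5%, 12 buildings cap the effective size at 12 / 0.025 = 480 per arm however many residents each holds, which gives about 18%.
- **Pairing on prior call rates and the baseline year could raise power.** They could, and repeat callers could lower it. Neither enters the stated calculation. To reach 80% for 10% with 700 per arm, the variance would have to fall by 1 − 700 / 3,385 ≈ 79% without clustering.
- **The word conservative might seem wrong.** It is not: 10% is smaller than the pilot's 25%. What fails is the claim that the stated number suffices for 10%.

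**Conclusion.** The point holds. The stated 131 per group is wrong on its own inputs by a factor of about 26 two-sided or 20 one-sided. At the stated minimum of 700 per arm in 12 buildings per arm, unadjusted, power for a 10% reduction is about 25% without clustering and 13% at the ICC ceiling (36% and 20% one-sided). The design has 80% power only for reductions of about 21% to 32%.

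This rests on reading the stated β as power, on one resident-year per resident, on Poisson variance multiplied by the usual design effect, and on equal building sizes. Sidedness changes the size of the shortfall but not its direction. The power range describes the minimum plan and is not a forecast for the trial as run. Nor is the whole design shown to be inadequate: for a reduction as large as the pilot's, the minimum plan has 91% power without clustering and 57% at the ceiling.

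**What to change.** In the Sample size section:

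1. Replace 131 with the figure that the inputs give (about 3,385 per group two-sided, before the design effect). State the sidedness, and write power 0.80 in place of β 0.8.
2. Restate, for the minimum of 700 per arm in 12 buildings, the power for 10% and the reduction detectable with 80% power over ICC 0 to 2.5%. If a gain from pairing or baseline adjustment is claimed, show it with its assumption.
3. Correct or remove the claim that 700 accommodates an ICC of 2.5% for a 10% effect, and give the number of residents per building used.
4. Stop presenting 10% as the powered effect. The remark that 10% is conservative relative to the pilot may stay.
5. Read the confidence interval already planned in the Data analysis section against the 10% operational threshold, so that a non-significant result is not taken to exclude it.

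The cost is a rewritten paragraph and a less favourable stated power. Recruitment does not have to change.
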